### 6.5.7 Report of Adverse Events

All adverse events must be recorded in the Case Report Forms (CRFs) and entered into the database. The records should include a general description of the symptoms and signs, the dates of onset and resolution, severity, relationship to the investigational vaccine or other medications, and measures taken to alleviate the symptoms.

If a participant experiences a serious adverse event (SAE) during the clinical trial, the investigator must immediately provide appropriate treatment to the participant.

Simultaneously, the investigator must complete a Serious Adverse Event Report Form (see Appendix 8) and report the event to the Safety Supervision Department of the National Medical Products Administration (NMPA) within 24 hours, with copies sent to the Registration Department, the sponsor, the ethics committee, and the higher-level health administration authorities. The report must include the rationale for diagnosing the event as an SAE and be signed and dated by the investigator. Grade 3 adverse events must be reported to the clinical trial sponsor within 2 working days after the decision is made.

### 6.5.8 Treatment of Adverse Events

When a participant experiences an adverse event during the clinical trial, the investigator at the clinical trial site must closely monitor the participant and provide appropriate treatment,

following these principles:

1. Immediate treatment for serious adverse events: Provide emergency care for serious adverse events (SAEs) without delay.

2. Discontinuation of immunization under the following circumstances:

- If the participant exhibits the following symptoms within 2 hours after vaccination:
  - Respiratory symptoms: including chest tightness, wheezing, palpitations, or difficulty breathing;
  - Circulatory failure symptoms: including pallor or cyanosis, bradycardia, weak or absent pulse, hypotension, hypothermia, or cold extremities;
  - Central nervous system symptoms: such as confusion, convulsions, or coma.
- If the participant experiences a grade 3 or higher systemic or local adverse event or laboratory abnormality related to vaccination.

3. Management of other adverse events: While conducting clinical observation and providing appropriate treatment, the timing of the participant's next vaccination should be postponed until the abnormal changes return to normal.

4. Handling adverse events after rTV vaccination: The assessment and management of adverse events following rTV vaccination should follow the principles for adverse reactions and management after smallpox vaccination (see Appendix 6).

In the event of a serious adverse event requiring emergency unblinding, the principal investigator of the clinical trial and the sponsor must jointly perform the unblinding.

## **6.6 Evaluation of Vaccine Immunogenicity**

### **6.6.1 Humoral Immune Response**

The following experiments will be conducted according to standard operating procedures:

1. Detection of HIV total antibodies and Env/Gag antibodies:

- Performed using the ELISA method.
- Confirmation of experimental results will be conducted by analyzing the following plate readings:
  - Specimens from all participants at the same time point.
  - Randomly selected specimens from the same participant at different time points.

2. Detection of HIV neutralizing antibodies:

- Performed using the TZM-bl method.

3. Detection of vaccinia virus binding antibodies:

- Performed using the ELISA method.

#### 4. Detection of anti-DNA and anti-nuclear antibodies:

- Conducted at Peking Union Medical College Hospital.

### 6.6.2 Cellular Immune Response

#### ELISPOT Assay:

- Performed using freshly isolated PBMCs from blood samples.
- Stimulation is conducted using peptide pools of Env, Gag, Pol, and Nef.
- Experimental results are measured using an automated plate reader.

#### Intracellular Staining:

- Performed using freshly isolated PBMCs from blood samples.
- Two detection methods are employed:

##### Method 1:

- Positive control: PMA + Ionomycin.
- Stimulation is conducted using peptide pools of Env, Gag, Pol, and Nef.
- Experimental results are measured using flow cytometry.

##### Method 2:

- Positive control: SEB.
- Stimulation is conducted using peptide pools of Env and Gag.
- Experimental results are measured using flow cytometry.

### 6.6.3 The storage of HLA testing specimens.

To facilitate further evaluation of cellular immune responses, peripheral blood samples from participants should be stored at the time of enrollment for HLA typing.

## 6.7 Early Study Termination

### 6.7.1 Subjects Early Withdrawal from the Study or Terminate the Vaccination

Subjects can withdraw from the study for any reason at any time. The study of the subjects should be terminated early in case of the following circumstances during the study. The study staff will need record the time and reasons of withdrawal in the original data table and transcribe them to CRF.

#### 1. Non-vaccination-related HIV antibody positivity:

- Stop subsequent vaccinations but continue follow-up.

#### 2. Pregnancy:

- For pregnancies occurring after all vaccinations are completed, follow-up should continue with the participant's consent to ensure their safety.

### 3. Adverse events following vaccination:

- If the participant exhibits the following symptoms within 2 hours after vaccination:
  - Respiratory symptoms: including chest tightness, palpitations, or difficulty breathing;
  - Circulatory failure symptoms: including pallor or cyanosis, bradycardia, weak or absent pulse, hypotension, or cold extremities;
  - Central nervous system symptoms: such as confusion, convulsions, or coma.
- If the participant experiences a grade 3 or higher systemic or local adverse event or laboratory abnormality related to vaccination.

### 4. Inability to participate in follow-up or specimen collection:

- If a participant's repeated inability to attend follow-ups or provide specimens significantly impacts data collection, the sponsor and clinical trial unit may decide to terminate their participation early.

For participants who withdraw due to adverse events, the reason and date of termination must be recorded on the adverse event report form and reported within 24 hours to the Safety Supervision Department of the National Medical Products Administration (NMPA), the sponsor, and the Institutional Review Board (IRB). Whenever possible, follow-up should continue until the expected end of the trial, but at least until the adverse event stabilizes or resolves.

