dose subgroup. Enrollment and vaccination will begin with the low-dose subgroup of the combined immunization group in the order of enrollment. The safety of the vaccine will be assessed within two weeks after each DNA vaccination in the low-dose subgroup. If no more than two vaccine-related adverse events of grade  $\geq 3$  (excluding fever above 39°C for no more than 3 days) occur, the trial will continue; if three or more such adverse events occur, subsequent vaccinations will be halted. Participants in both dose subgroups of the combined immunization group and the DNA-only group will receive three doses of 2 mg (low-dose subgroup) or 4 mg (high-dose subgroup) of the DNA vaccine at 4-week intervals. Enrollment and vaccination for the DNA-only group will commence simultaneously with the high-dose subgroup of the combined immunization group. If no more than two vaccine-related adverse events of grade  $\geq 3$  occur after each 4 mg DNA vaccination in the high-dose subgroup and the DNA-only group, the trial will continue; if three or more such adverse events occur, subsequent vaccinations in that dose subgroup will be stopped. If no more than two vaccine-related adverse events of grade  $\geq 3$  occur after the third DNA vaccination in each group, the combined immunization group will receive the rTV vaccine at the dose determined by the Phase Ia trial four weeks after the last DNA vaccination, while the DNA-only group will receive a placebo of the corresponding dose of the rTV vaccine. The placebo group will begin enrollment and vaccination at the same time as the low-dose subgroup of the combined immunization group and will receive placebos of the same volume as the DNA or rTV vaccines at the same time points. After the last vaccine or placebo administration, all participants will undergo at least six consecutive months of clinical and laboratory observation. In the Phase Ib trial, the interval between vaccinations in each group will be  $\geq 4$  weeks; if the time required for adverse reactions to heal or resolve exceeds 4 weeks, the interval between vaccinations will be  $\geq$  the actual time required for healing. The criteria for determining adverse events and their relationship to vaccination are detailed in Appendix 2 and Table 9.

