### 6.4.3 Determination of Success of rTV Vaccination and re-Vaccination

This trial uses the historical response to the Tian Tan strain vaccinia virus as a reference for the expected response following rTV vaccination.

Based on smallpox vaccination experience, first-time vaccine recipients typically exhibit a progression of skin reactions at the vaccination site, including papules, vesicles, pustules, scabs, and scab shedding, which generally takes about 3 weeks (see Appendix 6 for details). In individuals revaccinated with vaccinia virus, successful vaccination also follows this progression but with milder reactions and a shorter duration. For the rTV vaccine, the insertion of the HIV gene has significantly reduced the virulence of the Tian Tan strain vaccinia virus, and animal studies have shown that the toxicity of the rTV vaccine is 100–1000 times lower than that of the Tian Tan strain vaccinia virus. Therefore, the skin reaction induced by the rTV vaccine in humans may be milder than that of the Tian Tan strain smallpox vaccine. Additionally, due to technical issues, the vaccination site may only show mild needle trauma without the typical pustule formation, indicating vaccination failure.

For these reasons, rTV vaccination is considered unsuccessful if both of the following conditions are met:

1. The vaccination site shows no pustule formation as described above;
2. Serum vaccinia antibodies do not seroconvert (for individuals initially negative for vaccinia antibodies) or show no increase in antibody titer compared to pre-vaccination levels (for individuals initially positive for vaccinia antibodies) two weeks after vaccination.

In the Phase Ib trial, the data management center will unblind the clinical observers (while laboratory personnel remain blinded) on the third day after rTV vaccination to determine whether the rTV vaccination was successful. For individuals with unsuccessful rTV vaccination, a re-administration of the same dose will be performed on the contralateral upper arm four weeks after the first vaccination. Follow-up procedures after re-administration will follow the same protocol as after the initial rTV vaccination.

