### **6.10.4 Blinding Design**

Given that this trial includes a combined immunization group, a DNA-only group, and a placebo group, a blinded design will be implemented to prevent subjective bias among researchers during vaccination, clinical observation, and laboratory testing. However, since the reactions of participants before and after receiving the rTV vaccine and placebo are noticeably different, the blinding will no longer be effective for participants and clinical observers (but will remain effective for laboratory personnel) 3 days after the rTV vaccination.

In this Phase Ib trial, participants will be vaccinated with either the investigational vaccine or placebo under a blinded protocol. On days 3–4 after the last vaccination in each group, the blinding will be lifted jointly by the statistician, the principal investigator of the clinical trial, and the sponsor.

The blinding process will be carried out by personnel unrelated to the study, with assistance from the statistician, based on the random number table. This includes the preparation of blinded trial materials and emergency code-break envelopes. Each participant will be assigned a unique sequential number, with a corresponding blinded randomization code. After packaging the trial materials, the blinding codes will be stored in duplicate at both the clinical trial site and the sponsor's office.

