#### **6.10.7 Treatment of Missing Values**

In statistical analysis, missing values will not be imputed. Unless otherwise specified, all results are based on data with available analytical values.

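### Protocol 6.7.1 item 4 lets unblinded parties end participation for missed visits or specimens without keeping safety follow-up

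*Protocol*

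**What the plan says.** Section 6.7.1 lists circumstances in which a subject's study is to end early. The trigger in item 4 is: "If a participant's repeated inability to attend follow-ups or provide specimens significantly impacts data collection". The consequence is that "the sponsor and clinical trial unit may decide to terminate their participation early". The item gives no number of missed visits or specimens and does not say whether any follow-up continues.

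Other parts of the same section do address follow-up. For HIV antibody positivity unrelated to vaccination, item 1 reads: "Stop subsequent vaccinations but continue follow-up". Item 2 keeps follow-up, with consent, for pregnancies that occur after all vaccinations. The paragraph after item 4, which opens with participants who withdraw because of adverse events, adds: "Whenever possible, follow-up should continue until the expected end of the trial, but at least until the adverse event stabilizes or resolves".

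Elsewhere, section 6.4.2 says that after the last administration "all participants will undergo at least six consecutive months of clinical and laboratory observation". Table 3 defines the safety endpoint for the combined regimen as running from the first vaccination to 24 weeks after the last.

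On blinding, section 6.4.3 says that "the data management center will unblind the clinical observers (while laboratory personnel remain blinded) on the third day after rTV vaccination". Section 6.10.4 says of the unblinding that "the blinding will be lifted jointly by the statistician, the principal investigator of the clinical trial, and the sponsor", and it dates this step to days 3-4 following each group's final dose. Section 6.9.4 gives the same timing after rTV.

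On analysis, the safety set in 6.10.5(3) is every eligible subject with at least one dose, and 6.10.7 states: "In statistical analysis, missing values will not be imputed".

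**The concern.** Item 4 joins two different things: a gap in data, and the end of participation. The trigger covers attendance or specimens. As worded, a person who comes to every safety visit but repeatedly cannot give blood could be ended altogether, so that a specimen problem becomes the end of safety observation.

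The decision is discretionary and, for nearly all of the 24 weeks after rTV, it lies with parties who know the arm. This is the first human trial of the combination, the vector replicates, and safety is the primary objective. At stake is whether the 24-week safety record is complete, and whether anyone who knows the allocation can influence who remains in it.

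**Working it through.** The protocol states no figure on this point that could be reproduced, and it gives no dropout rate or late-event rate. The check is a comparison of texts, followed by illustrations.

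**1. Is follow-up kept?**

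| Circumstance | Follow-up stated |
|---|---|
| Item 1, HIV antibody positivity unrelated to vaccination | Yes |
| Item 2, pregnancy after all vaccinations | Yes, with consent |
| Withdrawal due to adverse events | Yes, where possible to the expected end of the trial |
| Item 4, repeated inability to attend or give specimens | Nothing stated |

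The sentence on continuing follow-up after item 4 is tied to the adverse event stabilizing or resolving. It belongs to its own paragraph and does not reach item 4.

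**2. Who knows the allocation?** Clinical observers know it from day 3 after rTV (6.4.3). The principal investigator, the sponsor and the statistician know it from days 3-4 (6.9.4, 6.10.4). Only laboratory personnel stay blinded. Both parties named in item 4 are therefore unblinded for all but the first few days of the 24 weeks. Decisions taken before rTV fall in the blinded period.

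**3. What does one termination after rTV remove?** Section 6.4.2 schedules visits at day 3 and weeks 1, 2, 4, 8, 12, 16, 20 and 24 after rTV, which is 9 visits. Weeks lost = 24 - t, where t is the week of the last visit attended.

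| Terminated after | Visits lost | Weeks lost |
|---|---|---|
| Week 2 | 6 of 9 | 22 of 24 (92%) |
| Week 4 | 5 of 9 | 20 of 24 (83%) |
| Week 8 | 4 of 9 | 16 of 24 (67%) |
| Week 12 | 3 of 9 | 12 of 24 (50%) |

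These are scheduled visits. Someone already missing visits would have attended fewer of them, so the table gives the most that termination itself can remove.

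**4. Weight of one person.** The arms are 12, 12, 6 and 6 (6.4.2, Table 5). 1/12 = 8.3% and 1/6 = 16.7%.

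**5. Effect on the reported rate (assumed numbers).** Suppose 2 of 12 in a dose group are terminated early and no event is seen in the group. Both stay in the safety set and nothing is imputed, so the reported rate is 0/12 = 0%. The true 24-week rate could lie anywhere from 0/12 = 0% to 2/12 = 16.7%.

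**6. Effect on what zero events can exclude (assumed numbers).** With n people fully followed and no events, the one-sided 95% upper limit is 1 - 0.05^(1/n). For n = 12 it is 22.1%, for n = 11 it is 23.8%, and for n = 10 it is 25.9%. The loss of precision is modest. The unseen events in step 5 matter more.

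**The case against.** **The trigger is narrow.** It requires repeated inability with a significant effect on data collection, and even then the text says only that termination may follow. A reader might infer that anyone who misses a visit can be removed; the wording does not support that. Those affected are already absent or not giving specimens, so termination itself may cost few visits. This stands, except for the person who attends but cannot give specimens.

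**Loss is not total.** A reader might infer a total loss of safety follow-up for people given a replicating vector. Data collected before termination are kept, dosed subjects stay in the safety set, later contact is not forbidden, and 12 of the 36 participants (DNA-only and placebo) never receive rTV. What is lost is the scheduled follow-up after termination.

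**The passages do not flatly contradict each other.** Section 6.4.2 sets the general schedule and 6.7.1 sets exceptions; subjects may also leave at any time for any reason. This stands. The passages need reconciling, but neither makes the other impossible.

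**Selection by arm is possible, not shown.** The trigger is attendance, not outcome. The time and reason of withdrawal must be recorded (6.7.1), monitors must confirm and record withdrawals and losses (7.3.3), and an independent board meets every two months (7.3.1). Laboratory staff stay blinded. Nothing in the protocol shows that reactions would cause the missed visits. These safeguards document a termination but do not restore the follow-up.

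**Vaccinia reactions are mostly early.** Annex 6 describes a local course ending by days 17-21 and systemic symptoms usually gone within two weeks, a period covered by visits and a four-week diary. This lowers the expected number of late rTV reactions. The same annex says, however, that the reactions to this vaccine can be determined only once the trial is complete, and Table 3 chose a 24-week window.

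**Conclusion.** The point holds in a limited form. Item 4 gives two parties, both unblinded from days 3-4 after rTV, discretion to end participation on an undefined criterion, and it does not keep the safety follow-up that other parts of the section keep. Scheduled follow-up after such a termination is lost, which fits poorly with the six-month observation of all participants and the 24-week safety endpoint.

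The size of the effect cannot be estimated. The percentages and visit counts above show what one or two terminations would mean under assumed numbers; they do not predict how many there will be. The conclusion rests on reading the adverse-event paragraph as not covering item 4, and on item 4 being applied as written. The matter belongs in the protocol, since it concerns who may end participation and what follow-up then remains. It is worth correcting because the correction is cheap, not because bias has been demonstrated.

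**What to change.** Amend item 4 so that the end of specimen collection is separate from the end of safety follow-up:

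- Missed visits and specimens are recorded as missing, and data already collected are kept.
- Safety follow-up, by any visit the participant can attend or by telephone, continues to 24 weeks after the last vaccination unless the participant withdraws consent.
- Add a cross-reference to 6.4.2 and Table 3 so that the three places agree.

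With no discretionary removal from safety follow-up, neither the sponsor nor the clinical trial unit can affect who stays in the safety data. Excluding only the sponsor from the decision would not achieve this, because the trial unit is equally unblinded. The rules on giving or stopping vaccination are left unchanged.

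The cost is one paragraph, a few telephone contacts by existing staff, and some incomplete profiles in the data set.

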## 6.7.2 Early Termination of the Clinical Study

In the low-dose combined immunization group, if three or more vaccine-related adverse events of grade  $\geq 3$  (excluding fever above 39°C for no more than 3 days) occur after each vaccination, the sponsor and the clinical trial unit should terminate subsequent vaccinations for all groups. However, follow-up for the affected participants should continue at least until the adverse events are resolved.

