## 6.9.4 Unblinding

In the Phase Ib trial, participants are enrolled and vaccinated with either the investigational vaccine or placebo under a blinded protocol. On days 3–4 after each rTV vaccination, once all relevant research data have been entered into the database, the blinding will be lifted jointly by the statistician, the principal investigator of the clinical trial, and the sponsor. In the event of a serious adverse event, the principal investigator of the clinical trial will perform an emergency unblinding using the emergency code-break envelope.

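### The low-dose halting rule differs between sections 6.4.2 and 6.7.2, and in the blinded first stage those who must apply it cannot see the count it needs

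*Protocol*

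**What the plan says.** Four statements govern when vaccination stops for a group. All of them count related adverse events of grade ≥3, with three or more as the trigger.

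- **Low dose, 6.4.2.** "The safety of the vaccine will be assessed within two weeks after each DNA vaccination in the low-dose subgroup". At three or more events, "subsequent vaccinations will be halted"; no groups are named. Fever above 39°C lasting no more than 3 days is not counted.
- **4 mg, 6.4.2.** With no more than two events after each 4 mg "DNA vaccination in the high-dose subgroup and the DNA-only group, the trial will continue"; with three or more, "subsequent vaccinations in that dose subgroup will be stopped". No window is given and the fever exclusion is not repeated.
- **Condition before rTV, 6.4.2.** If no more than two events "occur after the third DNA vaccination in each group, the combined immunization group will receive the rTV vaccine". No window is given and the fever exclusion is not repeated.
- **Low dose, 6.7.2.** Three or more events after each vaccination, with the fever exclusion and no window; then "the sponsor and the clinical trial unit should terminate subsequent vaccinations for all groups".

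On blinding, 6.9.4 says that "participants are enrolled and vaccinated with either the investigational vaccine or placebo under a blinded protocol". Section 6.10.3 randomizes the first 18 participants 2:1 to low dose or placebo, and the second 18 2:1 to high dose or DNA only. Section 6.10.4 lifts the blind on days 3–4 after the last vaccination. In Table 6, post-dose blood counts and liver and kidney chemistry fall at weeks 4, 8 and 12 during the DNA phase.

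**The concern.** These rules decide whether participants in the first human study of this combination go on to the next dose. Two people who read the protocol carefully should reach the same action from the same data. For low-dose events after day 14 of a DNA dose, or after rTV, they may not. Nor can the people named in 6.7.2 always tell whether the trigger has been reached, because they do not know which first-stage participants received vaccine. If this is settled during the trial, it will be settled after the events have been seen, and possibly by breaking the blind.

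**Working it through.** **No stated figure to reproduce.** The protocol gives no stopping probabilities, and 6.10.2 takes the sample size of 36 from the regulator's requirement. The allocation is consistent: 18 × 2/3 = 12 and 18 × 1/3 = 6 in each stage; 12 + 12 + 6 + 6 = 36.

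**Step 1: the rules on one dataset.** Suppose three related grade ≥3 events, none of them short fever, occur in the low-dose arm on days 15–28 after the third DNA dose.

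| Statement | Applies? | Action |
|---|---|---|
| 6.4.2, low dose | No, outside two weeks | Nothing stops |
| 6.4.2, before rTV | Yes, no window | Low-dose arm (12) does not go on to rTV, the implied converse of the condition |
| 6.7.2 | Yes, no window | All groups (36) stop |

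Events after low-dose rTV are a second case. Section 6.4.2 has no rule for them; 6.7.2 stops every group. This matters because Table 5 puts low-dose rTV at week 12 and high-dose rTV at week 14.

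**Step 2: counting unit.** Annex 2 grades DNA-site erythema, induration and swelling on separate rows, each Grade 3 above 3 cm, so one large reaction might count as one event or as three. Let *p* be the per-dose chance that a participant is affected. The documents give no value, so 5% and 10% are assumed. With X ~ Bin(12, *p*):

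- One event each needs three participants. P(X ≥ 3) = 1 − (0.5404 + 0.3413 + 0.0988) = 2.0% at 5%; 1 − (0.2824 + 0.3766 + 0.2301) = 11.1% at 10%.
- Two events each needs two participants. P(X ≥ 2) = 11.8% / 34.1%.
- Three events each needs one participant. P(X ≥ 1) = 1 − 0.95^12 = 46.0%; 1 − 0.90^12 = 71.8%.

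**Step 3: accumulation.** Take one event per affected participant and independent doses, over three DNA doses.

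- Count restarts at each dose: 1 − (1 − 0.0196)³ = 5.8%; 1 − (1 − 0.1109)³ = 29.7%.
- Count accumulates over 12 × 3 = 36 participant-doses: P(Bin(36, *p*) ≥ 3) = 26.8% / 71.2%.
- Accumulating, with affected participants discontinued as 6.5.8 and 6.7.1 require: each is affected at most once, with probability 1 − (1 − *p*)³ = 14.3% / 27.1%, giving P(Bin(12, ·) ≥ 3) = 23.9% / 67.2%.

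**Step 4: blinding in the first stage.** A blinded total of two or fewer events among the 18 rules out a trigger. At three or more the allocation is needed. If three participants are affected and risk is equal in both arms, the chance that all three are in the low-dose arm is C(12,3)/C(18,3) = 220/816 = 27.0%. The pooled count therefore does not show whether the rule is met.

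**Step 5: laboratory data.** Section 6.4.2 refers to Annex 2 for judging adverse events, and Annex 2 grades haematology and chemistry. Table 6 schedules neither at weeks 1–2, 5–6 or 9–10. The two-week assessment can therefore include no scheduled laboratory result obtained after the dose under review.

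**The case against.** Much can be said for the protocol.

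- **Scope.** A reader might infer that the two sections conflict over which groups stop. They can be read together: 6.4.2 names no group for the low dose, 6.7.2 supplies all groups, and the 4 mg rule stops only its own dose. The absence of a high-dose rule from a section on terminating the study is no contradiction. This objection stands. The conflict lies in the window, the vaccinations covered and the separate condition before rTV.
- **Blinding.** A reader might infer that every rule needs unblinded counts. The 4 mg rule names both second-stage arms and all 18 receive 4 mg DNA, so a pooled count needs no allocation. The data management center produces the randomization (5.3, 6.10.3), and codes are kept at the site and the sponsor's office (6.10.4). The information exists; what is missing is any statement of who uses it for these rules.
- **Events or participants.** Table 3 counts participants, which might suggest that counting events is an error. It is a design choice, and a cautious one. The gap is only that multiple signs in one person are not addressed.
- **Laboratory events.** Section 6.5.8 discontinues vaccination "If the participant experiences a grade 3 or higher systemic or local adverse event or laboratory abnormality related to vaccination". This is a rule for one individual and does not show what counts towards group halting; the link is the reference to Annex 2 in 6.4.2. Laboratory results at weeks 4, 8 and 12 remain available to 6.7.2, which has no window.
- **Individual protection.** Anyone with a related grade ≥3 event is discontinued under every reading, so the ambiguity concerns the remaining participants.

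**Conclusion.** The point holds as an inconsistency in the low-dose rule and a missing operator in the first stage. It does not show that the halting rules as a whole cannot be carried out. Low-dose events within two weeks of a DNA dose lead to the same action if 6.7.2 is taken to supply the groups stopped. Events after day 14, or after rTV, do not. In the worked example the action ranges from no group-level stop to 12 or 36 participants stopped. The short-fever exclusion is also unstated for the 4 mg rule and the condition before rTV, although fever above 39°C is Grade 3 in Annex 2.

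The probabilities are illustrations. They rest on assumed risks of 5% and 10%, a fixed number of events per affected participant and, across doses, independence. They show that the unsettled wording moves the chance of a trigger after one dose from 2.0% / 11.1% to 46.0% / 71.8%; they are not estimates for this vaccine. The blinding defect is confined to the first stage and to the per-group condition before rTV.

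**What to change.** Amend the protocol so that 6.4.2, 6.7.2 and the condition before rTV form one consistent statement covering:

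- the vaccinations covered and the window;
- whether counts restart at each dose or accumulate;
- whether several graded signs in one participant are one event or several;
- how short fever is handled under each rule;
- which groups stop.

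Reconcile the two-week assessment with the laboratory schedule in Table 6. Which clinical rule is adopted on each item is for the sponsor to decide.

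State that the data management center, which generates the allocation and already reports to the DSMB, supplies the arm-level counts for these decisions, with the blinded parties told only whether the threshold has been met. The DSMB's two-monthly meetings alone do not fit four-weekly dosing, so a report at each review is needed.

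The cost is amendment wording and that added data-center report. No further participants are required.
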